#### MICROFIT dietary component

2.6.4

Incorporating aspects of the Mediterranean diet alongside reduction of refined carbohydrate and sugar content and increase in healthier fats and proteins will be facilitated. Mediterranean diet has been shown to improve endothelial function with an increase in flow mediated dilatation (56, 57). Additional benefits of the intervention include a positive impact on lipid levels, insulin resistance and glycemic control (58–60) and reduction in systemic pro-inflammatory mediators (56, 61), all of which contribute to improved endothelial health.

The participants will undertake 1:1 sessions with a registered dietician, who will provide personalized advice and support upon review of pre-session combined photographic and written diet diaries. Incremental, achievable areas of improvement will be identified, with the dietician and participant collaborating to explore barriers to dietary change and potential solutions. The dietician will also continue to highlight the importance of smoking cessation, if applicable. The participants will be provided written guidance in form of an information booklet which they will be able to refer to throughout their participation in the study and beyond.

## Data analysis plan

3

### Blinding

3.1

The nature of the MICROFIT intervention prevents blinding of the participants and clinicians involved in their care to trial arm allocation. However, statistical and clinical outcome analyses will be completed blinded to study allocation.

### Data collection and management

3.2

#### Quantitative

3.2.1

Only secure NHS servers will be used to record and store patient identifiable data. Baseline and end of study data will be collected from trial assessments as per trial schedule, and it will be entered on site into an electronic case report form for each participant against participant unique identifier code, stored on NHS and University of Bath password protected computers. An electronic cross-referencing list will be stored on an NHS password protected computer database at each study site. Once collated, all data will be analyzed pseudonymously.

Assessment of the compliance with the exercise and dietary intervention will be assessed from exercise trainer and dietician records, stored on NHS password protected servers. Data will be collected regarding attendance at exercise and dietary intervention sessions, HR_max_ and RPE_max_ attained by participants during sessions, resistance training undertaken, biometric data and participants' self-reported adherence to prescribed home exercise.

##### MRI imaging

3.2.1.1

Quantitative stress perfusion MRI imaging and Oxygenation-Sensitive MRI (OS-CMR) sequence requires image transfer off-site for analysis. The MRI imaging acquired at St Joseph's Hospital in Newport will be securely transferred via Image Exchange Portal (IEP) to the sponsor site (the RUH) for analysis. The OS-CMR image analysis will be performed in a blinded fashion in a licensed core lab, using an automated tool (OCG19, Area19 Medical Inc., Montreal). The pseudonymized dataset will be transferred securely to the core lab (CMR Core Lab at McGill University Health Centre). This data will only be used for the purposes of this study and will not be retained for any other purpose. A data sharing agreement has been established between McGill University Health Centre as the partner and RUH as the sponsor for the trial. Similar contractual arrangement is being established with the Department of Cardiovascular Imaging at King's College London for transfer and core lab analysis of pseudonymized quantitative stress perfusion sequences.

#### Qualitative

3.2.2

Interviews with participants, practitioners delivering the MICROFIT programme, and healthcare professionals involved in CMD diagnostic pathway will be recorded, transcribed verbatim and stored on NHS servers against participant unique identifier code. All identifiable data, such as names of people or places, will be removed. Recordings will be deleted after transcription. Participants will be asked to provide consent to use verbatim quotes from the interviews in any subsequent publications.

All research records will be destroyed after ten years.

### Data analysis

3.3

Feasibility measures, namely the proportion of participants eligible, consented, randomised, and completing follow-up, will be reported with two-sided 90% confidence intervals calculated using the exact binomial method (ignoring site and strata). In the MICROFIT + Usual Care group, the proportion of participants adequately completing the intervention (as defined by the success criteria below) will also be reported.

The distributional properties of the continuous variables will be examined using graphical methods. Participant characteristics and all outcome measures will be summarized using descriptive statistics: mean (standard deviation) for normally distributed continuous variables, median [interquartile range] for skewed continuous variables, and number (percentage) for categorical variables. For longitudinal outcomes, mean (standard deviation) absolute and percentage change from baseline will be reported separately by trial arm allocation. A two-way analysis of covariance (ANCOVA), adjusted for baseline SAQ-7 score, will be used to analyze follow-up SAQ-7 scores to provide estimates of variability and effect size to support sample size calculations for a subsequent definitive randomized controlled trial. The target treatment difference for the definitive RCT will be based on a clinically important difference in the SAQ-7 and supported by existing literature and clinical consensus. Other exploratory outcomes will be summarized descriptively to estimate variability and inform the design of a future definitive randomized controlled trial. Additional exploratory inferential analyses may be undertaken where appropriate and will be interpreted cautiously in view of the feasibility nature of the study.

### Missing data

3.4

The analysis will be based on a complete-case per outcome basis. As this is a feasibility study, analyses of clinical outcomes are considered exploratory and will be interpreted cautiously. The extent and pattern of missing data will be described. Sensitivity analysis will be performed using multiple imputation after checking plausibility of the MAR assumption for SAQ-7 data only as the main secondary outcome which will form the basis of future power calculations.

A thematic analysis of the qualitative data collected through interviews will be undertaken.

### Success criteria

3.5

Feasibility will be assessed according to the following success criteria:
Recruitment rate: ≥40% of invited eligible participants consent to participate;Retention: ≥70% of the participants in both arms complete the study;Intervention adherence: ≥70% of MICROFIT participants complete ≥75% of sessions;Intervention acceptability: ≥70% of participants consider MICROFIT acceptable;Quantitative data collection methods are feasible and acceptable to participants, with no critical issues identified within patient-reported/qualitative data that contraindicate progression to RCT;Preliminary data on angina symptom-burden obtained to guide power calculations for subsequent RCT.Criteria 1–4 will be based on the lower 90% confidence limit (CL). The criteria provide guidance regarding progression to a full trial. Progression to a full trial will be considered if all of these targets are met. If any of the progression targets are not met but fall between 60% and 100% of the target then reasons for this would be considered by the trial management and advisory groups, which may result in changes being made to the trial design for the full trial. If any of the criteria fell below 60% of the target, then progression would not occur without significant and evidence-based changes to design. The specific targets and resultant recommendations for trial progression are outlined for each criterion in Table 1. Any decision to progress to a full trial will also take into consideration evidence from other concurrent research within the field.

**Table 1 T1:** Assessment of trial feasibility by success criteria analyzed by exact binomial method with 90% confidence interval.

Criterion	Progression to full trial	Consider progression to full trial, may need changes to design	Do not progress to full trial unless substantial change to design
	Lower limit of the 90% exact binomial confidence interval:		
Recruitment rate	≥40%	≥24%–39%	<24%
Retention rate	≥70%	≥42%–70%	<42%
Adherence rate	≥70%	≥42%–70%	<42%
Acceptability rate	≥70%	≥42%–70%	<42%

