#### Sample size

2.4.4

As this is a feasibility study, there is no primary outcome measure to inform a power calculation. The purpose of this feasibility study is to obtain empirical estimates to inform the design and progression criteria of the definitive multicenter trial. However, a sample size of 20 participants in each arm is sufficient to estimate feasibility outcome proportions for acceptability of 65% (90% CI: 44%–82%) and adherence rate of 85% (90% CI: 66%–96%) The corresponding intervals for recruitment rate will be more precise as the number of potential participants exceeds 40. The assumed recruitment, acceptability and adherence rates were planning assumptions informed by our local research experience from the prior *Super Rehab* trials (unpublished data), testing a similar lifestyle intervention in stable coronary artery disease and atrial fibrillation (37, 38), and published exercise intervention studies pertaining to ANOCA specifically (39–41), recognizing that this population may have a greater burden of symptoms.

A two-sided 90% confidence interval was prespecified because the principal interest in this feasibility study is the lower confidence limit for feasibility parameters such as recruitment and adherence. The lower limit of a two-sided 90% confidence interval is equivalent to a one-sided 95% confidence bound, which provides an appropriate assessment of whether these parameters are sufficiently high to support progression to a definitive trial.

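### At the plan's own planning rates, the expected acceptability and adherence results miss the Table 1 progression targets, because those targets apply to the lower 90% limit

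*Protocol article*

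**What the plan says.** Section 2.4.4 (Sample size) states that "a sample size of 20 participants in each arm is sufficient to estimate feasibility outcome proportions", and gives the planning values as "feasibility outcome proportions for acceptability of 65% (90% CI: 44%–82%) and adherence rate of 85% (90% CI: 66%–96"%). On their origin it says: "The assumed recruitment, acceptability and adherence rates were planning assumptions informed by our local research experience". It defends the 90% level by noting that "The lower limit of a two-sided 90% confidence interval is equivalent to a one-sided 95% confidence bound", and presents that bound as the test of whether a rate is high enough to go on to a definitive trial.

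Section 3.5 (Success criteria) sets the targets. For acceptability the target is "Intervention acceptability: ≥70% of participants consider MICROFIT acceptable". For adherence it is 70% of the MICROFIT group completing at least 75% of sessions. The section then adds "Criteria 1–4 will be based on the lower 90% confidence limit (CL"). Table 1 applies the same quantity, the lower limit of the exact 90% interval, to all three columns. For the 70% targets these are progress at 70% or more, consider from 42% to 70%, and do not progress without substantial redesign below 42%. Progression is considered only if every target is met.

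**The concern.** The two sections use the same statistic but do not agree. Section 2.4.4 prints the lower limits expected if the programme performs as planned. Section 3.5 sets a bar that both of those limits miss. For acceptability the assumed rate itself is under the bar, so no sample size would make a progress verdict likely at that rate.

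Feasibility is the primary objective, and Table 1 is how it becomes a recommendation. If a programme performing as planned almost never earns the progress verdict, that column says little about whether the plan worked. A second problem is that the lower limit also assigns the worst column. A low lower limit can reflect few participants as much as a low rate, so an imprecise result may be read as a poor one.

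**Working it through.** **Inputs.** From section 2.4.4: acceptability 65%, adherence 85%, 20 in the intervention arm. From section 3.3: two-sided 90% exact binomial intervals. From section 3.5 and Table 1: cut-offs of 70% and 42% (60% of 70%) on the lower limit, with all targets required.

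**Step 1: reproduce the printed intervals.** For x successes out of n, the exact limits are

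- lower = Beta quantile at 0.05 with parameters (x, n − x + 1)
- upper = Beta quantile at 0.95 with parameters (x + 1, n − x)

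65% of 20 is 13, which gives 44.2% to 82.3%. 85% of 20 is 17, which gives 65.6% to 95.8%. Both match the printed figures, so the method and n = 20 are confirmed for both criteria.

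**Step 2: place the expected results in Table 1.** The limits 44.2% and 65.6% both lie between 42% and 70%, so both expected results fall in the consider column.

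**Step 3: find the counts that separate the columns at n = 20.**

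| Count | Lower limit | Upper limit | Column |
|---|---|---|---|
| 12/20 (60%) | 39.4% | 78.3% | do not progress |
| 13/20 (65%) | 44.2% | 82.3% | consider |
| 17/20 (85%) | 65.6% | 95.8% | consider |
| 18/20 (90%) | 71.7% | 98.2% | progress |

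Progress needs X ≥ 18, and do not progress is X ≤ 12.

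**Step 4: verdict probabilities at the planning rates**, with X binomial (20, p).

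| | Progress, P(X ≥ 18) | Consider | Do not progress, P(X ≤ 12) |
|---|---|---|---|
| Acceptability, p = 0.65 | 0.012 | 0.589 | 0.399 |
| Adherence, p = 0.85 | 0.405 | 0.589 | 0.006 |

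The consider column is 1 minus the other two.

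**Step 5: both criteria together.** The probability that both reach progress cannot exceed the smaller of the two, 0.012. Under independence it is 0.405 × 0.012 = 0.005. The probability that at least one is do not progress is at least 0.399, and 1 − (0.601 × 0.994) = 0.403 under independence. Section 2.4.4 gives no numerical planning rate for recruitment or retention, so they are left out. Requiring them as well can only lower the chance of progress.

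**Step 6: sensitivity to the number giving an acceptability rating, at p = 0.65.** With 14 to 19 raters, do not progress has probability 0.44 to 0.58 and progress 0.005 to 0.021. With 40 raters the figures are 0.124 and 0.004.

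**Step 7: a true rate exactly on target.** If true acceptability were 70% with 20 raters, P(X ≥ 18) = 0.035 and P(X ≤ 12) = 0.228.

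**Step 8: the same cut-offs applied to the observed proportion** (progress at X ≥ 14, do not progress at X ≤ 8). At 65% acceptability these have probabilities 0.417 and 0.020. At 85% adherence, progress has probability 0.978. At a true 60%, progress rises from 0.004 under the lower-limit rule to 0.250.

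**The case against.** The best defence is that the rule is deliberately strict. Section 2.4.4 gives a reason for judging the lower limit: it guards against going forward on a chance high result. Step 8 shows what is lost by dropping it, since a programme with true acceptability of 60% would pass one time in four. A point-estimate rule would also leave acceptability short of progress 58% of the time at the planning rate (1 − 0.417), so it does not cure the mismatch. This stands, and it is why point estimates are not the required remedy. Strictness does not, however, explain planning on 65% against a 70% target.

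A reader might infer that the planning rates cannot reach the targets at all, or that a programme performing as planned is classed as a failure by construction. The document supports neither. Adherence at 85% reaches progress with probability 0.405. The expected results for both criteria sit in the consider column, which is also the most likely verdict for each. Section 3.5 describes the criteria as guidance, sends middle results to the management and advisory groups, weighs outside evidence, and lets even the worst column lead to progression after substantial redesign.

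The sufficiency statement in section 2.4.4 concerns estimating proportions. Read that way, the printed intervals support it. It would be wrong only if read as a statement about the decision rule.

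Minimum counts for retention and recruitment cannot be fixed from the article. Retention may be judged pooled or per arm, and consents may exceed 40 because consent precedes the baseline tests. No weight is placed on such counts here.

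**Conclusion.** The inconsistency holds and can be read directly from the printed figures: expected lower limits of 44% and 66% against a requirement of 70%, with one planning rate below the target even before uncertainty is considered. At the planning rates a progress verdict on both criteria has probability at most 1.2% under any dependence between them. A do-not-progress verdict on acceptability has probability about 0.40. Acceptability drives both figures; adherence contributes under 1% to the second.

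The 0.40 assumes that all 20 intervention participants give a rating, as the printed interval implies. It is 0.44 to 0.58 with 14 to 19 raters and 0.12 with 40. The bound on progress is less sensitive: P(progress) on acceptability stays at or below about 2% across those denominators.

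Using the lower limit alone for the do-not-progress column is a weakness in its own right. A result of 12/20 goes there although its upper limit of 78% is compatible with the 70% target. The consequence is softened by the guidance status of the criteria, but the thresholds as written do not fit the assumptions they were planned on.

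**What to change.** Before the adherence, retention and acceptability data are tabulated, the trial team should agree the following with the Trial Advisory Group:

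- Reconcile the planning rates in section 2.4.4 with the Table 1 targets, at minimum the 65% acceptability assumption against the 70% target.
- State in section 2.4.4 and Table 1 the minimum count for each column and the probability of each verdict at the planning rates. Name the denominators assumed for retention (pooled or per arm) and for acceptability (who gives a rating).
- Limit the sufficiency statement in section 2.4.4 to precision of estimation.
- If the lower-limit rule is kept for progress, base the do-not-progress column on the observed proportion or the upper limit, not on the lower limit alone.

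Applying the progress cut-offs to observed proportions, with the exact interval reported beside each, is an option. Its price is the weaker protection shown in step 8 (0.25 against 0.004 at a true 60%).

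The cost is wording in sections 2.4.4 and 3.5 and in Table 1, with no new data or participants. Timing matters: section 4.2 reports over three quarters of participants enrolled, so recruitment data are largely accrued. Any change to the recruitment criterion should be dated and declared as made with that knowledge.

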## Trial management

4

### Ethical approval

4.1

Ethical approval was granted by Plymouth and Cornwall Research Ethics Committee (IRAS project ID 340782, reference: 24/SW/0125, 30th October 2024). Further substantial amendment to the trial protocol (to include a qualitative sub study on patient and healthcare practitioners' experience of the diagnostic pathway to CMD) has been approved on the 28th of March 2025. Written informed consent will be required from the participants prior to enrolment in the study.

### Study status

4.2

Recruitment for the study began on 2nd December 2024. With over three quarters of expected participants already enrolled, closure of recruitment is expected in October 2026. Follow up and participant involvement is expected to continue until May 2027.

### Study governance

4.3

The Trial Management Group (TMG) will be led by one of the Co-Chief Investigators (AK, DT) and will comprise the full research team. The TMG will meet monthly and oversee day-to-day management of the study, including monitoring of adverse events and trial progress. A Trial Advisory Group (TAG) will take on the roles usually held by a trial steering committee and data monitoring committee and will be led by an independent consultant cardiologist, with expert input from an external consultant cardiologist with clinical and research interest in cardiac MRI imaging and exercise physiology, and PPI lead. The TAG will be joined by co-chief investigators and the study coordinator (JA) to update on progress. The TAG will be consulted for advice (e.g., regarding decisions for specific study procedures and processes, including adverse events), and will meet regularly, with a view to prepare for a subsequent multicenter RCT.

### Adverse events

4.4

Adverse events (AEs) and serious adverse events (SAEs) will be documented throughout the study, including the final follow-up. AEs will be reviewed during TMG meetings, discussed with the TAG, and reported to the sponsor and research ethics committee in accordance with their respective guidelines.

### Patient and public involvement (PPI)

4.5

PPI for the trial is provided by the NHS Research and Development office for Bath, Swindon and Wiltshire (BSW). Feedback from the BSW “PARTICIPATE” group and a local cardiovascular disease-focused PPI group informed development of the trial. Patient representatives contributed to refining participant-facing materials, including the participant information sheet. Ongoing PPI will be coordinated by the PPI lead, who organized engagement sessions with individuals affected by coronary artery disease or microvascular dysfunction, participates in the TAG, and supports dissemination through events and newsletters. PPI input will also inform site selection for a future RCT and the development of the definitive trial grant application.

### Results dissemination

4.6

Upon trial completion, participants will be offered the opportunity to discuss their individual results with the study cardiologist. Anonymized trial findings will be disseminated through peer-reviewed journals, national and international conferences, and local primary and secondary care networks to raise awareness of CMD and support improved diagnosis and treatment. Results will also be shared at NHS Research & Development public dissemination events in BSW.

## Discussion

5

MICROFIT is a feasibility randomized controlled trial of a structured lifestyle intervention comprising HIIT, resistance training and dietary counselling in patients diagnosed with CMD. The advantage of this multimodal programme over previously reported unidimensional interventions (10) is that this combination targets specific risk factors for CMD (such as obesity, sedentarism, hypertension, metabolic syndrome) and provides a comprehensive secondary prevention intervention for patients with the disease, delivered as a credible, cardiologist-led programme within a community setting. The intervention follows a progressive three-phase structure with gradually tapering levels of supervision. This design aims to facilitate the transition from supervised activity to sustainable ongoing self-management and addresses the limited duration of support that has characterised previous exercise interventions in patients with CMD (10). The programme incorporates evidence-based behaviour change techniques, which further enhances the likelihood of success and ongoing engagement beyond the programme (32).

A key strength of the MICROFIT study is its rigorous phenotyping of participants. Unlike previous lifestyle intervention studies, which have often relied on clinical suspicion of ANOCA (10, 25), eligibility requires invasive coronary function testing confirming CMD, defined by impaired coronary flow reserve (CFR <2.5) and/or acetylcholine flow reserve (AChFR ≤1.5). This diagnostic approach reduces population heterogeneity and increases confidence that any observed effects target a well-characterized population with confirmed CMD.

The multicenter design, incorporating recruitment from both a district general hospital and tertiary cardiac center, enhances the generalizability of the findings and provides an opportunity to evaluate the feasibility and deliverability of the intervention across different NHS settings, where a future definitive RCT would be set. The SAQ-7 was selected as the proposed future primary outcome because it is a validated, disease-specific measure of angina symptoms, physical limitation, and health-related quality of life (62, 63). As the principal aim of lifestyle intervention in patients with CMD is to reduce symptom burden and improve functional status, a patient-reported outcome is considered the most clinically relevant primary endpoint. Mechanistic measures, including cardiopulmonary exercise testing (64–66), quantitative stress perfusion CMR (28) and the novel OS-CMR (29, 31), will complement these findings by providing exploratory insight into the physiological mechanisms underlying any observed symptomatic benefit.

A delivery of a 24-week-long, multicenter and multidimensional intervention, alongside relatively extensive baseline and follow up investigations, does present operational challenges. The research team has substantial experience in delivery of similar lifestyle intervention programs, which helped inform the design of this study, including sample size planning (based on recruitment and attrition rates seen previously), trial locations and personnel selection and training. This extensive experience, alongside research team's engagement in national NIHR-BHF CMD Workstream network, will be of advantage for planning of the future definitive RCT.

The trial requires high levels of engagement from participants, not least due to intensity of the intervention itself, but also attendance at baseline and follow up visits. Patient and public involvement has been embedded throughout the study, informing the development of participant-facing materials, intervention delivery, and ongoing trial oversight. Informed by the PPI input, the trial strives to streamline the study visits to lessen the burden on the participants, and community and online delivery of the intervention aims to improve recruitment rates and retention. This collaborative approach is expected to improve the acceptability, relevance, and feasibility of the intervention and trial procedures.

Overall, the MICROFIT study will provide important evidence regarding the feasibility, acceptability and delivery of a comprehensive lifestyle intervention for patients with invasively confirmed CMD, while generating preliminary estimates of clinical outcomes. These findings will inform the design of a future adequately powered multicenter randomized controlled trial, aiming to address a largely unmet need of this understudied population.
